**Abbreviations and acronyms**

AIDS-Acquired Immunodeficiency Syndrome

ART- Antiretroviral treatment T

CDA- Complete Diagnostic Autopsy

CDC- Center for Disease Control and Prevention

CHC- Carmelo Hospital of Chokwé

CM-Cryptococcal meningitis

CNBS- National Bioethics Committee for Health

CNS-Central Nervous System

CrAg- Cryptococcal antigen

CSF- Cerebrospinal fluid Cerebrospinal fluid

DAP-Dynamic Adaptation Process

HIV - Human Immunodeficiency Virus

HP-Health professional

ID - Patient identification

IFI - Invasive Fungal Infections

JMGM- José Macamo General Hospital

MCH- Maputo Central Hospital

MGH- Mavalane General Hospital

MoH -Ministry of Health

NHS-National Health System

OR-“Odds Ratio”

RDT- Rapid diagnostic test

UEM-Universidade Eduardo Mondlane

USA- United States of America

US-Unidade Sanitária

VD-Dependent variable

WHO-World Health Organization

**Abstract**

In the world, cryptococcal meningitis (CM) associated with HIV infection has been identified as the cause responsible for around 150,000 - 200,000 deaths per year, occurring mainly in the sub-Saharan African region, with a record of over 70%; 135,900 [95% CI 93,900-163,900]. Limitations in the diagnosis and treatment of patients with HIV-associated CM may be the probable cause of the high mortality rate in the sub-Saharan African region.

The World Health Organisation (WHO) recommends screening and treatment of cryptococcosis in all HIV patients in order to avoid complications and reduce the mortality rate. However, in countries with limited resources, there is a need to implement diagnostics that are appropriate to the country's reality, simple and inexpensive in order to avoid missing diagnostic opportunities due to rapid test breakdowns. The India ink technique in urine has been indicated as an alternative for the diagnosis of Cryptococcus, as urine can easily detect the presence of this pathogen, especially in individuals with disseminated infection.

The main objective of the study is to implement the India ink technique in urine for point-of-care laboratory screening of cryptococcosis in adult HIV-infected patients in southern Mozambique.

A stepped wedge trial of scientific implementation with a mixed approach will be carried out. Sampling will be non-probabilistic by convenience and intentional. Data collection will be done through questionnaires, observation, and semi-structured interviews with health professionals (clinicians and laboratory technicians). Implementation will be in phases and a Dynamic Adaptation Process (DAP) conceptual framework will be used then the intervention will be evaluated using the RE-AIM (Reach, Effectiveness, Adoption, Implementation, and Maintenance) conceptual framework.

It is hoped that the findings of this study will provide advocacy so that the Ministry of Health (MoH) can prioritize diagnostic strategies with low-cost non-invasive samples and maximize the diagnosis, control, and prevention of CM which, together with HIV, are devastating the country's health and socio-economic resources.

# Motivation

During the coordination of surveillance of invasive fungal infections (IFI) at Maputo Central Hospital, there were challenges related to the diagnosis and breakdown of the rapid tests currently in use, which is a limitation for the timely diagnosis of cryptococcosis. In addition, diagnosis using an invasive CSF sample has been a barrier in places with few health professionals with the skills to collect the sample. The India ink technique in urine is simple and less expensive and has been indicated as an alternative for diagnosing Cryptococcus.

IFIs have recently taken center stage among the diseases that affect the health and well-being of the population worldwide. With the advent of HIV/AIDS, IFI is one of the main causes of consultation, hospitalization, and death, especially in sub-Saharan Africa. Studies show that prolonged treatment with antibacterials without a cure is probably caused by fungi. Mortality from cryptococcosis is practically inevitable in the absence of proper diagnosis and treatment. Gaps in care and diagnosis can contribute to poor management of fungal infections, especially in Mozambique where they are neglected.

According to data from INSIDA 2021, the prevalence of HIV in the adult population in Mozambique is 12.5%(1). HIV is a risk factor for IFIs, and in Mozambique, the most complex IFI diagnosis is carried out at the Central Hospitals and academic reference laboratories of the Department of Microbiology at the Faculty of Medicine of Universidade Eduardo Mondlane (UEM). The priority is to implement a diagnosis of cryptococcosis that is appropriate to the country's reality, simple and inexpensive, in order to avoid missed diagnostic opportunities due to the breakdown of rapid tests and to improve the management of IFIs in the context of care and treatment, which has been little done.

The introduction of timely non-invasive diagnosis, its promotion, and its expansion to cover a greater proportion of HIV patients suspected of having cryptococcosis can contribute to starting treatment closer to the time of admission, improve patient outcomes, and contribute to reducing mortality.

# Objectives

2.1. **Main objective**

- Evaluate the implementation of the India ink technique in urine as a point-of-care laboratory screening technique for cryptococcosis in adult HIV-infected patients in southern Mozambique.
- 2.2. Specific objectives
- To analyze the existing practices and challenges in the laboratory diagnosis of cryptococcosis in the following hospitals MCH, MGH, JMJH, MPH, XPH, and CHC;
- Implement the technique of laboratory diagnosis of cryptococcosis using the India ink method in urine as a point of care in the selected hospitals;
- To evaluate the reach, efficacy, adoption, implementation, and maintenance of the India ink method in urine as a point-of-care laboratory diagnosis for cryptococcosis.

# Contribution

Providing acceptable healthcare in sub-Saharan Africa is a complex process, due to the scarcity of human and material resources and extremely limited access to diagnostic tests.

Each year, approximately 12 million people die in sub-Saharan Africa (2,3) and most of these deaths are not investigated. The few deaths that are investigated are generally attributed to infectious diseases (4), most commonly HIV infection, malaria and tuberculosis.

In the absence of laboratory confirmation, the accuracy of these estimates remains uncertain.

In Mozambique, due to the growing number of people at risk of cryptococcosis combined with various factors including HIV, the introduction of timely, less expensive cryptococcosis diagnosis with a non-invasive sample (urine) and a result on the same day as the consultation, could contribute to an increase in laboratory confirmation of suspected cryptococcosis cases and guide clinicians with an aetiological diagnosis to start treatment. It could be expanded to the country's peripheral hospitals, contribute to diagnosis and treatment in patients where invasive samples are not accessible, and allow treatment to be started as soon as the patient is admitted.

The implementation is also intended to be sustainable, used for continuous (routine) screening, and to alleviate socio-economic resources in the country.

# Problem

Sub-Saharan Africa has the highest burden of invasive/opportunistic infections associated with HIV/AIDS (5). Cryptococcosis is an important opportunistic infection and one of the main causes of consultation and hospitalization in adults living with HIV in sub-Saharan Africa (6).

In Mozambique, approximately 2,097,000 (two million and ninety-seven thousand) adults are living with HIV, with a prevalence of 12.5%, according to data from INSIDA 2021(1).

The classic diagnosis of cryptococcosis is carried out by testing for the microorganism in cerebrospinal fluid (CSF) or blood. Invasive samples are currently being replaced by alternative non-invasive samples that are easy to obtain and have shown the same performance without harming the patient. Studies show that there are gaps in the diagnosis of fungal infections associated with non-comprehensive diagnosis of cryptococcosis, limited access to rapid diagnostic tests (RDTs), especially in developing countries, and that little has been done to improve progress in diagnosis (7,8).

In Mozambique, IFI is neglected and data is very scarce. Few published studies estimate the annual incidence of cryptococcal meningitis (CM) at 18,600 cases (70.5 cases per 100,000 people/year), and the country ranks third among the countries with the highest incidence of CM (8,9). The recently published study using complete diagnostic autopsy (CDA) in 284 deceased patients from Mozambique (n=223) and Brazil (n=61) showed that Cryptococcus was responsible for 16 deaths among the 163 HIV-positive patients (10%; 95 % CI: 6-15%), including four maternal deaths (6).

More accurate non-invasive diagnosis at the time of admission can improve patient outcome and contribute to reducing mortality from cryptococcosis.

## Research questions

# What opportunities exist to implement the point-of-care diagnostic technique for cryptococcosis in the context of care and treatment of cryptococcosis in HIV patients?

# What factors contribute to the reach, efficacy, adoption, implementation, and maintenance of India ink as a point-of-care diagnostic technique for cryptococcosis in the selected hospitals?

# Literature Review

Worldwide, data published up to 2021 showed that HIV-associated CM was responsible for 150,000-200,000 deaths a year(10). These deaths occurred mainly in sub-Saharan Africa, where mortality was over 70%; 135,900 [95% CI 93,900-163,900] (7,9,10,11). One of the main reasons for this high mortality is the delay in diagnosis, associated with limited access to lumbar puncture and diagnostic tests(13). In this region, studies show that despite efforts to provide antiretroviral treatment (ART), there is an increase in the burden of opportunistic invasive infections, including cryptococcosis (13,14).

Most HIV-associated infections are caused by *Cryptococcus neoformans*, although in Botswana, up to 30% of infections are caused by *Cryptococcus gattii(*11).

CM is among the most underfunded diseases in the world. It has recently been proposed as a neglected tropical disease (15). It is believed that prolonged treatment with antibacterial agents and failure to cure HIV patients with headaches and fever is probably caused by Cryptococcus spp (16,17). Death from CM is practically inevitable in the absence of adequate treatment (5).

The prevalence of specific fungal pathogens depends on their endemicity. Recently published studies show that 70% of all cryptococcosis cases in some African countries appear to support HIV diagnosis and approximately 30% after the start of ART (18,19).

Early identification of cryptococcal infection is extremely crucial (20). Screening, early treatment and intervention have been shown to be viable for reducing the course of the disease and deaths from CM in HIV/AIDS patients (14). In sub-Saharan Africa, providing acceptable healthcare has been a major challenge due to the scarcity of resources and extremely limited diagnostic tests (7).

The diagnosis of cryptococcosis has been carried out in the past using a sample of cerebrospinal fluid (CSF) with India ink and isolation of the yeast in Sabouraud dextrose culture medium. However, urine is currently a highly desirable sample for the diagnosis of cryptococcosis in places with limited resources, few doctors, and other health specialists mainly in primary-level hospitals (18,21), particularly when there are difficulties in obtaining invasive samples such as blood or CSF. Cryptococcus spp in urine is an indicator of disseminated cryptococcosis(22). In the majority of cases in the country, CSF is collected by specialized clinicians.

Urine samples have the potential to increase the chance of early diagnosis of cryptococcosis in many settings, as they are easy to obtain (18,23).

Studies have shown agreement of results (sensitivity and specificity) using invasive samples (blood and CSF) when compared to non-invasive samples (urine) in the diagnosis of cryptococcosis (18,24). Saha et al. (24) in their findings found a positive predictive value ranging from (82.9, to 100%) for china ink using urine samples, which suggests a good test for screening. This diagnostic method has a sensitivity of (85-86.1%) and a specificity of 100%, and the result is obtained on the same day as the sample is taken.

The WHO (25) and other studies published by Greene et al., 2020 and Stott et al., 2021 recommend the use of cryptococcal antigen (CrAg) testing for cryptococcosis screening in patients living with HIV. However, some studies show the unsustainability of CrAg in relation to costs in low-income countries when compared to India ink and also public hospitals show more confidence in the most commonly used diagnostic means for cryptococcosis, India ink and culture (26,27).

Cryptococcosis is an opportunistic mycosis that is transmitted by inhaling viable propagules of Cryptococcus spp. The fungus is found in the environment, in pigeon droppings, eucalyptus and decaying organic matter (13,28). The yeast has two recognised varieties Cryptococcus neoformans var. neoformans (serotypes A, D and AD), which causes over 90% of infections, and Cryptococcus neoformans var. gattii (serotypes B and C). The grubii variant has recently been described and is related to serotype A. The fungus has a sexual or teleomorphic phase which consists of the formation of basidiospores (29). In the parasitic phase, i.e. in the tissues, the microorganism appears as a capsulated yeast and sometimes with budding. When inhaled, the fungus first reaches the lungs where it can be latent in alveolar macrophages or proliferate with tropism for the central nervous system (CNS), causing CM (28,29).

Currently, cryptococcosis has gained greater prominence and its incidence has increased with the emergence of HIV. The increase in the incidence of IFIs is associated with the growing number of patients with risk factors for these infections. Other conditions and associated risk factors are: neutropenia, diabetes mellitus and kidney infection, intensive care hospitalization, use of immunomodulators, extensive surgery or burns, and invasive interventions (12).

Patients with cryptococcosis present with headache and fever with an average duration of two weeks between the onset of symptoms and the first signs. Many patients develop nausea, vomiting, diplopia due to cranial nerve paralysis (CN VI), and reduced visual acuity related to high CSF pressure. If left untreated, symptoms progress to an abnormal mental state, reduced level of consciousness, seizures, and finally coma (11).

Clinically significant invasive disease is associated with the reactivation of latent infection among immunocompromised individuals, such as people living with HIV, months to years after initial exposure (13).

With regard to treatment, according to the World Health Organisation (WHO) and the Centre for Disease Control and Prevention (CDC), the antifungal intravenous amphotericin B and oral fluconazole have been shown to be effective for the treatment of cryptococcosis (25,30). The WHO recommends treating asymptomatic cryptococcal infection with oral fluconazole and close monitoring in order to reduce possible side effects (25).

# Conceptual framework

This study will be guided by the conceptual framework called the Dynamic Adaptation Process (DAP) that will support the implementation of the non-invasive diagnostic method for cryptococcosis in the selected hospitals and another called RE-AIM with five domains (Reach, Effectiveness, Adoption, Implementation and Maintenance) to evaluate the implementation (Figure 2). The PAD involves identifying essential elements and adaptable features (barriers and facilitators) based on evidence, supporting implementation with specific training on adaptations allowed to the model, monitoring fidelity, and supporting and identifying the need and solutions for adapting workflow in the context of cryptococcosis care and treatment (31,32).

Fidelity refers to an assessment of the adherence and competence of health professionals. Adherence to the diagnosis of cryptococcosis with non-invasive sampling that will be implemented in this study meets the expectations of the model's creators and will be measured as one of the intervention's indicators. The ability of health professionals to use the model is called competence. The PAD model has four implementation phases (pre-implementation, adaptation, implementation and evaluation), takes into account the multi-level context of service delivery, involves various stakeholders and provides knowledge and continuous feedback. During the intervention, it guides and provides ‘steps’ for monitoring the implementation of the diagnosis.

[figure not shown]

# Methods

## Study design and type

The study design is a stepped wedge trial with a mixed approach. Stepped wedge studies are prospective and intervention studies. The main characteristic of these studies is that the researcher sets up the implementation in phases, monitors the conditions of the intervention, and makes it possible to assess the effectiveness of the intervention tool or technique implemented. This type of study ensures that all selected study sites eventually receive the intervention and generally provides more reliable evidence (See Table 1).

**Tabela 1. Desenho de estudo *Stepped-wedge***

| Phases | Months/2024-2025 | | | | | | | | | | | | | | |
| --- | --- | --- | --- | --- | --- | --- | --- | --- | --- | --- | --- | --- | --- | --- | --- |
|  | 1 | 2 | 3 | 4 | 5 | 6 | 7 | 8 | 9 | 10 | 11 | 12 | 1 | 2 | 3 |
| MCH | C | C | C | C | PI | AD | I | FU | FU | FU | FU | FU | FU | FU | FU |
| MGH | C | C | C | C | PI | AD |  | I | FU | FU | FU | FU | FU | FU | FU |
| JMGH | C | C | C | C | C | PI | AD |  | I | FU | FU | FU | FU | FU | FU |
| MPH | C | C | C | C | C | PI | AD |  |  | I | FU | FU | FU | FU | FU |
| XPH | C | C | C | C | C | C | PI | AD |  |  | I | FU | FU | FU | FU |
| CHC | C | C | C | C | C | C | PI | AD |  |  |  | I | FU | FU | FU |

**C-** Control**; PI**-Pré-implementation; **AD**- Adaptation; **I**-Implementation; **FU**- follow-up

The mixed method approach will allow triangulation and complementarity of the findings, giving the possibility of strengthening the research conclusions (33). The quantitative part will be cross-sectional and the qualitative part will be generic. Quantitative data such as (the number of tests carried out with Chinese ink, positive results, negative results, response time, level of academic education of health professionals, number of health professionals allocated to HIV services, number of trained professionals, percentage of services that adhered to the intervention, number of microscopes in existence) will be obtained through a questionnaire administered to health professionals and by observation based on the previously drawn up script.

In the qualitative part, through semi-structured interviews, topics will be explored that address (challenges for: diagnosis, and treatment of cryptococcosis, and the satisfaction of health professionals in relation to the intervention will also be evaluated).

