## Study timeline

- The study will last approximately 1 year and 3 months with different phases:
- First phase: Assessment of the current situation: (duration 3 months):
- Second phase: Adaptation (duration 3 months);
- Third phase: Implementation of the intervention in phases guided by the PAD (duration 6 months);
- Fourth phase: Evaluation, sustainability and results according to the RE-AIM (duration 3 months).

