# To implement the technique of laboratory diagnosis of cryptococcosis using the China ink method in urine as a point of care in selected hospitals in three southern provinces of Mozambique.

This is a stepped wedge trial. Sampling will be non-probabilistic by convenience in relation to the study sites and purposive in relation to the participants.

The study will be carried out in six hospitals (MCH, MGH, JMGH, MPH, XPH, and CHC) over six months. The Adaptation Phase will be the beginning of the iteration with the new test, the healthcare professionals (clinicians in medical service and laboratory technicians assigned to the microbiology sector) adapt to the workflow associated with the intervention (Figure 2). During the three months of adaptation, the researcher will carry out training on the care, diagnosis and treatment of cryptococcosis using urine dye (5 to 20 ml of the sample) with intentionally selected healthcare professionals, the diagnostic guide tools will be provided and an information-sharing workflow will be established between the laboratory and the clinicians.

It's up to the clinician to decide which patients to ask for a urine sample to diagnose cryptococcosis and also to decide what clinical information to share with the laboratory according to each situation. We will provide the national health system with a resource for the diagnosis of cryptococcosis, instead of empirical treatment when routine treatment is not available. Therefore, the clinician is free to request routine or experimental testing. If the clinician decides to request a urine sample for the diagnosis of cryptococcosis, the laboratory will provide feedback according to the clinician's request in order to follow up on the patient.

The implementation of the diagnosis of cryptococcosis with Chinese ink using non-invasive urine samples at the selected sites will take place over 6 months. In this implementation phase, the health professionals assigned to the medical service with knowledge of the intervention (new test for cryptococcosis) will request that it be carried out by colleagues from the laboratory who have been previously trained in its execution. Throughout this phase (Figure 2) monitoring of clinicians' behaviour in relation to the use of the new diagnostic will take place and documentation of its implementation will be captured (Appendix V).

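### As labelled in Table 1, all control months end before the first implementation month, so control versus intervention is aliased with calendar time

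*Protocol*

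**What the plan says.** Section 7.1 of the protocol states: "The study design is a stepped wedge trial with a mixed approach". It justifies the choice by saying that the design "makes it possible to assess the effectiveness of the intervention tool or technique implemented", and adds that such studies give more reliable evidence.

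Table 1 gives the schedule. The first hospital to start reads "MCH | C | C | C | C | PI | AD | I | FU", a middle one "JMGH | C | C | C | C | C | PI | AD", and the last "CHC | C | C | C | C | C | C | PI | AD". The legend codes control separately from pre-implementation and from the later phases ("AD- Adaptation; I-Implementation; FU- follow-up"). Nine cells between adaptation and implementation carry no code.

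Three other places bear on how the cells should be read:

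- Sub-study 1 describes pre-implementation (PI) as an assessment of the situation before the intervention is put in place.
- Sub-study 2 describes adaptation (AD) as the first contact with the new test: "During the three months of adaptation, the researcher will carry out training on the care, diagnosis and treatment of cryptococcosis". Diagnostic guides and a laboratory-clinician workflow are supplied at the same time.
- Sub-study 3 says that efficacy will be evaluated before and after implementation.

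Section 7.3 lists four phases of 3, 3, 6 and 3 months, beginning with "First phase: Assessment of the current situation: (duration 3 months"). It names no control period.

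**The concern.** A stepped wedge earns its credibility from months in which some hospitals already use the intervention while others do not. Those months let the analysis remove whatever is changing everywhere at once. If control time ends everywhere before the intervention starts anywhere, that comparison is missing and the study becomes before versus after.

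This matters here because background change is plausible on the protocol's own account. Its Motivation section names breakdowns in rapid-test supply as the problem to be solved. A shift in test supply, staffing or season around month 7 would look the same as an effect of urine India ink on time to diagnosis or laboratory results. This is a property of the schedule. A statistical analysis plan could not repair it using the cells marked control and exposed unless it assumed a shape for the time trend.

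**Working it through.** The protocol gives no power or precision figure for the stepped wedge, so there is none to reproduce. The check uses Table 1 alone.

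**Step 1: code the grid (6 hospitals x 15 months = 90 cells).**

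| Hospital | C | PI | AD | unlabelled | I | FU |
|---|---|---|---|---|---|---|
| MCH | 1-4 | 5 | 6 | none | 7 | 8-15 |
| MGH | 1-4 | 5 | 6 | 7 | 8 | 9-15 |
| JMGH | 1-5 | 6 | 7 | 8 | 9 | 10-15 |
| MPH | 1-5 | 6 | 7 | 8-9 | 10 | 11-15 |
| XPH | 1-6 | 7 | 8 | 9-10 | 11 | 12-15 |
| CHC | 1-6 | 7 | 8 | 9-11 | 12 | 13-15 |

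Counts: C 30, PI 6, AD 6, unlabelled 9, I 6, FU 33; 30 + 6 + 6 + 9 + 6 + 33 = 90.

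**Step 2: C against I/FU.** The last C is month 6 and the first I is month 7. Among these 30 + 39 = 69 cells, exposure x equals 1 exactly when the month is 7 or later, so x = M7 + M8 + ... + M15, where Mt is the indicator of month t. The matrix of 15 month indicators plus x has 16 columns and rank 15. With hospital effects added, the rank is 20 without x and 20 with it. The effect is not estimable with free month effects.

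**Step 3: other readings of the cells between C and I.** Exposed is I/FU throughout. Inflation is the within-hospital sum of squares of x divided by what remains after month effects are also removed, with cells weighted equally.

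| Counted as unexposed | Months with both conditions | Rank without x, with x | Inflation |
|---|---|---|---|
| C | none | 20, 20 | not estimable |
| C + PI | 7 | 20, 21 | 17.98 / 0.61, about 29 |
| C + PI + AD | 7-8 | 20, 21 | about 12 |
| C + PI + AD + unlabelled | 7-11 | 20, 21 | 20.93 / 4.67, about 4.5 |

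In the second row, the overlap is XPH and CHC (both in PI) against MCH.

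**Step 4: are the later cells clean?** AD delivers training, guides and a new workflow, and the unlabelled months come after it. Neither is an untouched control. Some of the unlabelled cells may be the continuation of a merged AD cell, because the text gives adaptation three months and the table shows one AD cell per hospital. On that reading they are still adaptation time, so the conclusion is the same.

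**Step 5: the repaired schedule.** Place AD in months 6, 7, 8, 9, 10 and 11 in table order, and leave PI and I where they are. Unexposed hospitals while another is in I or FU:

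- month 7: JMGH, MPH, XPH, CHC (4)
- month 8: MPH, XPH, CHC (3)
- month 9: XPH, CHC (2)
- month 10: CHC (1)

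The total is 4 + 3 + 2 + 1 = 10, or 8 if the two PI cells in month 7 are left out. With hospital and month effects the rank rises from 20 to 21, so the effect is estimable.

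**The case against.** The strongest reply is that the aliasing is not complete. PI is only an assessment, so it is unexposed on the protocol's own description, and month 7 then holds both conditions. This stands. A reader might infer from Table 1 that no concurrent comparison exists on any reading, and the documents do not support that. What remains is one month with two hospitals against one.

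A second reply is that AD and the unlabelled months can also serve as unexposed, which restores overlap through month 11. On precision alone this reading does no worse than the repaired schedule: after hospital and month effects, exposure keeps a sum of squares of 4.67 against 3.19. A reader might therefore infer that moving the training dates itself buys precision. It does not. Its value is that the control months precede training, whereas trained months used as control would tend to dilute the contrast. The protocol gives no record counts or intracluster correlation, so no standard error is offered.

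Third, a linear time trend would make C against I/FU estimable. It would do so by extrapolation, with inflation of about 7.0.

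Two further inferences go too far. The gaps from AD to I (1, 2, 2, 3, 3 and 4 months) might suggest that later hospitals start with older training, but this fails if the blanks are merged AD cells. Section 7.3 might seem to leave no unexposed time, since 3 + 3 + 6 + 3 = 15 fills the study. However, its first phase is a pre-intervention assessment, and its first three durations also match the spans of PI (5-7), AD (6-8) and I (7-12) across hospitals. The defect there is that section 7.3 omits the control period and does not match Table 1.

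Finally, sub-study 3 openly plans a before-after evaluation, and most aims are implementation measures. That limits the damage to the effectiveness claim but does not support that claim.

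**Conclusion.** The point holds for Table 1 as labelled. All 30 control cells fall in months 1-6 and all 39 implementation or follow-up cells in months 7-15, so with unrestricted month effects the contrast is fully aliased with calendar time. Treating PI as unexposed leaves a single month of overlap. Any wider overlap relies on months after training has begun, which the legend does not call control.

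The schedule therefore does not support the effectiveness claim made in section 7.1, and the before-after comparison in sub-study 3 cannot separate the intervention from background change. This rests on the table's own month labels and on sub-study 2's account of adaptation. It does not depend on how the blank cells arose or on any assumed sample size or correlation.

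**What to change.** Keep PI, every implementation month and the study length. Then:

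1. Move AD to the month just before each hospital's I: MCH 6 (unchanged), MGH 7, JMGH 8, MPH 9, XPH 10, CHC 11.
2. Label the months before AD, other than PI, as C, and collect the same outcomes in them as in the exposed months. State that PI counts as unexposed.
3. Treat AD as a transition month left out of the effect estimate.
4. Include hospital and calendar-month terms in the effect model; without the month term the new overlap is not used.
5. Reconcile Table 1 with section 7.3, which should name the control period and show the phases overlapping, and with the three months of adaptation in sub-study 2, which can be read as the staggered span across hospitals.

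If the dates have already passed, state which cells count as control and describe efficacy as an uncontrolled before-after comparison, without the stepped-wedge effectiveness claim.

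Cost: training at five hospitals moves later by 1 month (MGH, JMGH), 2 months (MPH, XPH) or 3 months (CHC). There are six separate trainings instead of three pairs, and some monthly data collection that the protocol does not clearly plan now.
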